### Safety

Supervised exercise will be performed with continuous heart rate monitoring. If the heart rate of a participant increases to ≥80% of their heart rate reserve, the exercise will be stopped. Any adverse effects including but not limited to dizziness, extreme breathlessness, extreme fatigue, chest pain, or falls during exercise or after a session will be documented and assessed by study staff to decide if the event is related to the exercise. In addition, subjects feeling discomfort while participating in the intervention will receive appropriate treatment.

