### Intervention

All participants will continue with their prescribed medication. They will attend the same weekly educational sessions including on quitting smoking, self-management, and nutrition. In addition, participants in the exercise groups will attend 3 exercise sessions over 2 weeks to become familiar with the intervention programs. During this study time, the participants will be given oral and visual instructions on how to perform the prescribed pulmonary exercises or the exercises with elastic bands and will be given instructions on how to perform the exercises at a Borg CR10 intensity level of between 4 and 6 [23]. In addition, all participants in the exercise groups will receive a teaching video and exercise record book. After each exercise session, participants will be required to record what they have done, including but not limited to time, duration, intensity, and site (home or other).

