#### Control group

Participants in the CG will continue with their prescribed medication and will not receive the exercise intervention.

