#### Pulmonary exercise group

Participants in the PG will continue with their prescribed medication treatment and receive 3 months of prescribed pulmonary exercise. The PG exercise regimen will comprise sessions twice daily, 7 days per week over 3 months. On Sunday afternoons, the participants will exercise under the supervision and instruction of physiotherapists in a group format. Each of the these sessions will last approximately 60 min and consist of (1) a 10-min warm-up exercise, focusing on the flexibility of the peripheral skeletal muscles; (2) 40 min of prescribed pulmonary exercise consisting of eight characteristics including the “hu” and “si” sounds in *liuzijue*, “pushing up the sky to regulate the triple warmer” and “drawing a bow to shoot a vulture” in *baduanjin*, “the crane actions, including the crane spreading its wings and flying” in *wuqinxi*, and “cross-armed iron staff” in *yijinjing*; and (3) a 10-min cool-down exercise focusing on stretching the peripheral skeletal muscles. Exercise intensity will be self-determined as being between 4 and 6 according to the Borg CR10 scale (meaning patients feel the intensity as somewhat strong to very strong when performing the exercise). Their heart rate will be monitored using a Polar Team^2^ (Polar, Finland).

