### Adherence

For patients in the CG, compliance will be quantified by the number of responses to telephone calls conducted once a week by the specialist, with compliance defined as no less than 85%. In other words, there should be no fewer than 11 responses. For patients in the three intervention groups, compliance will be quantified by the completion of the exercise log by patients and attendance at the supervised training sessions in the hospital. Compliance will be defined as no less than 85% of exercise sessions completed.

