The study has some limitations. First, in any study with an exercise intervention, it is difficult to blind the therapists and participants, so there may be a placebo effect leading to biased results. Lack of blinding may also lead to a deviation from the intended intervention, with participants possibly seeking other treatments during the trial; however, methods such as keeping a log of exercise sessions and completing questionnaires on physical activity may be useful in identifying this. Second, the study mainly focuses on a home-based exercise intervention, and participant compliance may be lower than with a supervised outpatient intervention. However, designated staff will contact participants and supervise the extent of intervention through checking their exercise log books and by telephone. Third, the prescribed pulmonary exercise adopted in the study is a form of traditional Chinese exercise, so that knowledge about is restricted geographically, which may hinder its application and promotion. Finally, the participants included in the study are from the same hospital, so the study results will need to be confirmed by a multi-center study.

In conclusion, this article presents the design and protocol of a clinical trial investigating the effects of home-based prescribed pulmonary exercise in patients with stable COPD. The results of this study are expected to confirm the effects of prescribed pulmonary exercise in COPD patients and identify the strengths and shortcomings of prescribed pulmonary exercise, exercising with elastic bands, and a combined exercise program. In addition, the results may provide the basis for new, operable, effective, and home-based COPD PR programs.

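### The one stated adverse-effect rule is triggered by exercise sessions, so, followed as written, it ascertains events unequally across the four arms

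*Protocol article*

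**What the plan says.** The Safety section of the protocol article is the only place that describes how harm is recorded. It covers "Any adverse effects including but not limited to dizziness, extreme breathlessness, extreme fatigue, chest pain, or falls", and those occurring "during exercise or after a session will be documented and assessed by study staff to decide if the event is related to the exercise". The list of event types is open. The occasion for recording is an exercise session, and the question put to staff is whether exercise was the cause.

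The Control group section says that these participants "will not receive the exercise intervention". Their planned contacts are two. Under Intervention, all participants share weekly education: "They will attend the same weekly educational sessions including on quitting smoking, self-management, and nutrition". Under Adherence, for the control group, "compliance will be quantified by the number of responses to telephone calls conducted once a week by the specialist". Neither place mentions asking about events.

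The exercise arms have more channels. Under Intervention, "all participants in the exercise groups will receive a teaching video and exercise record book", and the Discussion adds that "designated staff will contact participants and supervise the extent of intervention through checking their exercise log books and by telephone".

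Acute exacerbation appears under Participants as an exclusion criterion. It is not listed under Outcome measurement, and the Safety section does not name it.

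**The concern.** A recording rule that starts from an exercise session has nothing to start from in an arm without sessions. Dizziness, breathlessness, fatigue, chest pain and falls can all plausibly occur without exercise in patients aged 40 to 80 with stage II to IV COPD. To know how many such events the exercise programmes add, one needs the number that occur under usual care, collected in the same way. Without it, the reader of the results has only a staff judgement of relatedness, made with knowledge of the exercise and with no comparator.

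Two things are at stake. First, a table of events by arm could show an excess in the exercise arms that comes from recording alone. Second, if exercise reduced exacerbations or admissions, the trial could not show it. Both matter for a programme that the article hopes to offer for home use and that is supervised on one day a week. Exacerbations may also affect walking distance, spirometry and drop-out, so uneven knowledge of them makes the primary outcomes harder to interpret.

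**Working it through.** **Arm size (context only).** The Sample size section gives a difference of 54 m, an SD of 57 m, 80% power and two-sided 5% alpha. With the normal approximation, n = 2 × (1.96 + 0.84)² × 57² / 54² ≈ 17.5, rounded up to 18 per group, as stated. Adding 20% gives 18 × 1.20 = 21.6, rounded up to 22 per group, and 4 × 22 = 88. The point below does not depend on this calculation; it uses only the 22 per arm.

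**Recording occasions under the stated rule.** The inputs are the weekly session numbers in the four intervention sections. For example, for the pulmonary exercise group, "The PG exercise regimen will comprise sessions twice daily, 7 days per week over 3 months". Three months is taken as 12 to 13 weeks (an assumption).

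| Arm | Sessions per week | Sessions over 12 to 13 weeks |
|---|---|---|
| Control | 0 | 0 |
| Resistance | 3 | 3 × 12 = 36 to 3 × 13 = 39 |
| Pulmonary | 2 × 7 = 14 | 14 × 12 = 168 to 14 × 13 = 182 |
| Combined | up to 14 + 3 = 17 | up to 17 × 12 = 204 to 17 × 13 = 221 |

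The combined arm reaches 17 only if its pulmonary and resistance sessions are counted separately. The trigger is absent in one arm, and it occurs more than four times as often with pulmonary as with resistance exercise (14 / 3 ≈ 4.7).

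**What recording alone could do (assumed rates, not in the article).** Suppose the true proportion of patients with an event is the same in all arms, every event is recorded in the 3 × 22 = 66 exercise patients, and none is recorded in the 22 controls. This is the extreme case.

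| Assumed rate | Recorded, exercise | Recorded, control | Expected but unrecorded, control | Fisher p |
|---|---|---|---|---|
| 10% | 7/66 | 0/22 | 22 × 0.10 = 2.2 | 0.19 |
| 20% | 13/66 | 0/22 | 22 × 0.20 = 4.4 | 0.03 |
| 30% | 20/66 | 0/22 | 22 × 0.30 = 6.6 | 0.002 |

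The p-values only gauge how large an artefact could look. The article plans no such test.

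**What equal recording could achieve.** With 22 against 22 and assumed true rates of 20% and 40%, power is about 30%. Equal recording would therefore not turn this into a safety trial.

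**The case against.** The strongest reply is that this is a condensed article. It does not say that events outside sessions go unrecorded, and all-arm event forms may stand in a fuller protocol. The section on adherence defines how control-group compliance is counted and leaves the content of the calls open. The section on data management refers to medical records, from which exacerbations or admissions might be taken. No aim, outcome or planned test compares adverse-event rates, and a relatedness judgement on session events is a coherent, if narrow, purpose.

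Much of this stands, and it rules out several stronger readings that a reader might infer:

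- **That control-group events will never be recorded, or that the calls serve only to count answers.** The article does not say so. It only makes no provision for systematic recording, and a stray event might still be noted.
- **That events away from a session are missed in the exercise arms.** The phrase about events after a session has no time limit. With sessions twice a day, every day, in the pulmonary and combined arms, almost any event there follows one. This makes the imbalance with the control group larger.
- **That harm cannot be compared between arms at all.** The dyspnoea scale, spirometry and the respiratory questionnaire with its symptoms domain are assessed in all participants at baseline and 3 months. Respiratory worsening can be compared on these, although they are not event counts.

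The reply does not remove the point. The article is not silent on safety. It states a rule, and the rule's scope differs by arm. An analysis plan could not repair this later, because events that were not collected in one arm cannot be analysed.

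**Conclusion.** The point holds as one of unequal ascertainment. The only stated rule depends on exercise sessions, which number 0, 3, 14 and up to 17 per week in the four arms, and nothing in the article provides equivalent recording in the control group. If the rule is followed as written, event counts by arm are not comparable, and background events cannot be separated from those due to exercise.

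This rests on reading the Safety section as the full recording rule, which is an inference from its scope and from the absence of any other procedure. The size of any resulting artefact depends on event rates that the article does not give: over assumed rates of 10% to 30%, about 2 to 7 control-group patients with events would go unrecorded in the extreme case. The sample size and the planned efficacy tests are not affected. This is a cheap improvement to the description of harms, not a flaw in the main comparison.

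**What to change.** Change the Safety section so that all adverse events, including exacerbations and hospital admissions, are recorded from randomisation to 3 months in all four arms. Use the same short question set on the same weekly schedule: in the control group through the weekly calls already planned, and in the exercise arms through the staff contact already planned. The interval of that contact is not stated for the exercise arms, so set it to weekly to match.

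Report the number of events and the number of patients with at least one event, descriptively, by randomised arm. Keep the judgement of relatedness to exercise as an additional item, made after an event has been recorded and not as a condition for recording it.

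The cost is slightly longer calls, one form and one table. No treatment, session schedule or efficacy outcome changes.

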### Data management

The medical records and data collected from participants will be stored securely. Only authorized research assistants will have access to the trial data.

## Discussion

The study expects to investigate the effects of prescribed pulmonary exercise on lung function, exercise capacity, skeletal muscle function, quality of life, and psychological function in stable COPD patients, and is expected to produce a comprehensive understanding of the effects of prescribed pulmonary exercise on COPD patients by comparing (1) usual care, (2) pulmonary exercise, (3) exercising with elastic bands, and (4) pulmonary exercise combined with exercising with elastic bands.

In terms of completion rate, a previous study based on a 6-month home-based *baduanjin* exercise intervention (including four sessions led by a trained therapist) in COPD patients (FEV1%pred: 37.12 ± 2.22) had a drop-out rate of 35% [11]. Another study of a *liuzijue* exercise intervention in COPD patients (FEV1%pred: 41.5 ± 4.5) with a similar protocol had a drop-out rate of 6% [8]. A 12-week home-based tai chi exercise intervention for COPD patients (FEV1%pred: 59 ± 16) had a drop-out rate of 10% [34]. The differences in the completion rate in previous studies may be attributed to various factors, including the duration of the intervention, the number of guidance sessions, differing content, and disease severity. Although the drop-out rates varied, a high completion rate for our traditional Chinese exercise intervention is predicted. In addition, drop-out rates for elastic band training protocols performed by COPD patients are in the range 15–25% for intervention protocols ranging in length from 8 to 12 weeks [19, 21, 22]. Hence, an assumed drop-out rate of 20% is feasible for this this study.

Dyspnea, the main complaint of COPD patients, can limit exercise capacity and impair skeletal muscle function, further aggravating dyspnea to form a vicious cycle [3]. Therefore, treating dyspnea and improving exercise capacity and skeletal muscle function in COPD patients are important.

As a gentle, self-healing, and functionally intact exercise, traditional Chinese exercise includes key characteristics of isometric contraction, stretching, relaxation, and adjustment of body posture combined with breathing techniques, with the main purpose of strengthening the body. A meta-analysis has shown that traditional Chinese exercise is a low-to-medium intensity exercise, suitable for middle-aged and elderly COPD patients with positive effects on lung function (indicated by improved FEV1 and FEV1/FVC), exercise capacity (6MWT) and quality of life [7]. A growing number of studies have attempted to explore the effects of this novel application of traditional Chinese exercise in preventing and controlling chronic diseases. Prescribed pulmonary exercise is based on the basic theory of traditional Chinese medicine and targeted to COPD rehabilitation using a reorganization of *liuzijue*, *wuqinxi*, *baduanjin*, and *yijinjing*. Liu et al. [12] found that rearranged traditional Chinese exercises could improve the activity of life and social participation significantly [12]. Since the study mainly focused on lung function, exercise capacity, activity of life, and inflammatory factors in COPD patients, the effects on skeletal muscle function and physical activity are unclear. Hence, this study aims to investigate the effects of prescribed pulmonary exercise in COPD patients using multidimensional indicators.

Exercising is the best available method of improving skeletal muscle function, and is considered as the cornerstone of PR for COPD [35]. Resistance exercise (achieved by various means, including with apparatus, bodyweight lifting, and elastic bands), as an important component of PR, can significantly improve skeletal muscle mass and function. It can be used to counterbalance skeletal muscle dysfunction [3]. Previous studies have found that resistance exercise (including with bands and conventional resistance exercise) has significant effects on improving fat-free body mass [19, 36] and skeletal muscle strength (assessed by digital dynamometry) in COPD. An additional benefit of improved exercise capacity (6MWT) was found when exercising with elastic bands compared with conventional resistance exercise [19]. An elastic band is made of natural latex, which is a cheap, lightweight, and portable material that can be safely applied by the subjects themselves. The use of bands is not limited by time or place. Hence, we wish to investigate the effects of exercising with elastic bands by COPD patients and compare it with the effects of prescribed pulmonary exercise, to clarify the specific effect and role of prescribed pulmonary exercise for stable COPD.

The main characteristic of exercising with resistance bands is an improvement in skeletal muscle function and exercise capacity by providing resistance to target muscle groups. Pulmonary exercise combines posture and breathing training, as a whole-body aerobic exercise, which may be effective in improving dyspnea and aerobic exercise capacity. It is possible that the combination of these two exercise modalities will have complementary effects in COPD patients, compared with a single exercise type. Hence, the study will combine prescribed pulmonary exercise with exercising with resistance bands for COPD patients, and compare the effects with each single exercise modality, to investigate this simple, convenient, home-based, and effective exercise for COPD patients.

There are several highlights to this study. First, the prescribed pulmonary exercise is a rearrangement of traditional Chinese exercise and targeted to COPD patients. The effects of this prescribed pulmonary exercise on lung function, respiratory muscle strength, exercise capacity, skeletal muscle function, quality of life, and physical activity on stable COPD patients will be evaluated. Second, the role of prescribed pulmonary exercise in improving skeletal muscle function and exercise capacity will be determined by comparing the effects of pulmonary exercise and an elastic band program. Third, the effect of pulmonary exercise combined with exercising with elastic bands in stable COPD patients will be determined, and the effects compared with a single program to determine whether combined exercise can achieve additional beneficial effects. Fourth, the study will apply comprehensive measurements to evaluate skeletal muscle function in patients with COPD, including isokinetic muscle strength testing, surface myoelectricity, 6MWT, and the 30-s arm curl test. Fifth, a sub-analysis will be performed to investigate if the treatment effects differ in patients with different disease severity to enable the optimization of treatment effects for all patients suffering from the troublesome disease. Finally, the study is in strict accordance with CONSORT guidelines, so that the effects of the prescribed pulmonary exercise can be clearly determined.

The study has some limitations. First, in any study with an exercise intervention, it is difficult to blind the therapists and participants, so there may be a placebo effect leading to biased results. Lack of blinding may also lead to a deviation from the intended intervention, with participants possibly seeking other treatments during the trial; however, methods such as keeping a log of exercise sessions and completing questionnaires on physical activity may be useful in identifying this. Second, the study mainly focuses on a home-based exercise intervention, and participant compliance may be lower than with a supervised outpatient intervention. However, designated staff will contact participants and supervise the extent of intervention through checking their exercise log books and by telephone. Third, the prescribed pulmonary exercise adopted in the study is a form of traditional Chinese exercise, so that knowledge about is restricted geographically, which may hinder its application and promotion. Finally, the participants included in the study are from the same hospital, so the study results will need to be confirmed by a multi-center study.

In conclusion, this article presents the design and protocol of a clinical trial investigating the effects of home-based prescribed pulmonary exercise in patients with stable COPD. The results of this study are expected to confirm the effects of prescribed pulmonary exercise in COPD patients and identify the strengths and shortcomings of prescribed pulmonary exercise, exercising with elastic bands, and a combined exercise program. In addition, the results may provide the basis for new, operable, effective, and home-based COPD PR programs.

### Trial status

The trial was registered in July 2018 and is currently in the recruitment phase.

## Abbreviations

%pred: Percentage of the predicted value
6MWT: 6-min walking test
ANOVA: Analysis of variation
ATS/ERS: American Thoracic Society / European Respiratory Society
CG: Control group
COPD: Chronic obstructive pulmonary disease
DXA: Dual-energy X-ray absorptiometry
FEV1: Forced expiratory volume in 1 s
FVC: Forced vital capacity
GOLD: Global Initiative for Chronic Obstructive Lung Disease
mMRC: Modified Medical Research Council Dyspnea Scale
PASE: Physical Activity Scale for the Elderly
PG: Pulmonary exercise group
PR: Pulmonary rehabilitation
PRG: Pulmonary exercise and resistance exercise group
RG: Resistance exercise group
sEMG: Surface electromyography
SES: Chronic Disease Self-Efficacy Scale
SGRQ: St. George’s Respiratory Questionnaire
